### Adjuvants

AS01B contains 50 g of MPL®, 50 g QS21 (QS21 is a triterpene glycoside purified from the bark of *Quillaja saponaria*) and liposomes.

## Dosage and administration

Reconstitution of vaccines with AS01B and administration:

Group 3: 1 vial of Final Container FMP010, Lot 1157

Disinfect top of a vaccine vial with the antigen cake with alcohol swabs - let dry.
Aspirate the contents of the AS01B vial with a syringe and inject adjuvant into the vial of lyophilized antigen and remove needle from vial.
Dissolve the cake by gently shaking the vial. Wait for approximately one minute to ensure complete dissolution of vial contents before withdrawing 0.5 mL of the reconstituted vaccine solution using a fresh needle and syringe.

Group 4 (Rabipur® rabies vaccine): Rabipur® rabies vaccine is a licensed vaccine and will be prepared in accordance with the package insert.

Each vaccine dose should be administered by slow intramuscular injection in the deltoid muscle of the non-dominant arm within four hours of reconstitution. Prior to each vaccination, the non-dominant arm will be inspected for clinically evident physical findings that might interfere with post-vaccination assessment of reactogenicity. If such a finding is discovered, the dominant arm may be used at the discretion of the investigator.

The vaccines will be administered in the Muriithi Wellde Clinical Trials Centre (Part B) under the supervision of physicians skilled in the management of anaphylactic reactions.

Vaccine and adjuvant vials will be labeled with subject identifier and saved until study completion and discarded upon instructions from GSK Biologicals.

### Treatment allocation

Volunteers will be randomized to the candidate vaccine or the control arm when they present for vaccination 1.

## Storage

- All vials containing FMP010 will be stored at 2-8oC.
- All AS01B vials must be stored at 2-8oC.
- Rabies will be stored at 2-8oC.
- Storage temperatures will be recorded daily.
- Records must be maintained that document receipt, release for vaccination, disposal, or return, to the manufacturer of all vaccine vials.

### Packaging: See Appendix D

### Accountability: See Appendix D

### Replacement of unusable vaccine doses

Additional doses of vaccine and adjuvant will be provided to replace those that are unusable (see Appendix E for details of supplies). In case a vial or pre-filled syringe is broken or unusable, the person in charge of the vaccination will use a replacement dose. Although the sponsor need not be notified immediately in these cases, documentation of the use of the replacement dose and reason for using it must be recorded by the investigator on the vaccine administration page of the CRF and on the vaccine accountability form. Proper disposal of syringes will occur after each dose administration. Spent vaccine vials/ pre-filled syringes, labeled with the volunteers’ identification number, will be retained separately for confirmation of correct dosing if need be

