**Method of blinding**

The sponsor will generate a randomization list which will be made available to the study site and both the local medical and the WRAIR medical monitors prior to the onset of the study.

Data pertaining to FMP010/AS01B or control vaccines will be collected in a double blinded (observer blind) manner. ‘Double blinded (observer blind)’ means that the vaccine recipient as well as those responsible for the evaluation of study endpoint data will all be unaware which treatment, FMP010/AS01B or control vaccine, was administered to a particular subject. The vaccines in this study are of different volumes. The contents of the syringe will be masked with an opaque label to ensure blinding. The only study staff aware of the vaccine assignment for FMP010/AS01B or control vaccine will be those responsible for preparation of the vaccines; these staff will play no other role in the study which would require clinical evaluation.

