**Replacement of unusable vaccine doses**

If a vaccine dose needs replacement, the envelope with the corresponding treatment number will designate the replacement without unblinding the study

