**2. Vaccine packaging**

The vaccine will be packed in labeled boxes. The box label will contain the following information: study number, subject number, lot number, and instructions for vaccine administration.

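### The investigator who rates safety must also record replacement doses and their reasons, and such an entry can reveal the arm

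*Protocol*

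**What the plan says.** **Who may know the arm.** Section 5.4, Method of blinding: "The only study staff aware of the vaccine assignment for FMP010/AS01B or control vaccine will be those responsible for preparation of the vaccines". These preparers take no part in clinical evaluation. The next paragraph keeps the investigator blind even when the local medical monitor unblinds a participant.

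**Replacement, first description.** Section 5.4, in the paragraph on unusable doses: "the envelope with the corresponding treatment number will designate the replacement without unblinding the study".

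**Replacement, second description.** Section 6.3.3: "Additional doses of vaccine and adjuvant will be provided to replace those that are unusable". When a vial or syringe cannot be used, "the person in charge of the vaccination will use a replacement dose". The use and the reason "must be recorded by the investigator on the vaccine administration page of the CRF and on the vaccine accountability form". No envelope, treatment number or preparer is mentioned.

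**Who rates safety.** Section 8 makes the investigator responsible for detecting and documenting adverse events. Section 8.3 has the investigator judge causality for everything except solicited local reactions, which count as related by rule.

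**Supplies.** Appendix D lists 60 vials of FMP010 and 60 of AS01B, with three spares of each. It lists no Rabipur stock. Either an investigator or a pharmacist may sign for receipt, and the counts of supplied, used and remaining doses must agree at any time.

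**The concern.** The protocol gives a product-related record to a person who is meant to be blind. A separate adjuvant vial exists only in the FMP010 arm, so recording why a dose was replaced, or updating a count of what was used, can disclose what the volunteer received. This is a records route to unblinding. The opaque syringe label does nothing about it.

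Safety and reactogenicity are the primary objective, in a comparison of 20 against 10 volunteers. Headache, fatigue, nausea, malaise, myalgia, joint pain and injection-site pain are graded by judgement, and so is the causality of all but the solicited local reactions. Once a rater knows a volunteer's arm, the later judgements for that volunteer are no longer blind. A replacement at dose 1 affects nearly the whole follow-up. One at dose 3 affects only what comes after it.

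**Working it through.** **1. Supply figures.** The inputs are 20 volunteers in Group 3, 10 in Group 4 and three doses each (Study Design Overview), with 60 vials and 3 spares per component (Appendix D, item 1).
- Group 3 need: 20 × 3 = 60 antigen vials and 60 adjuvant vials, as stated.
- Spares: 3 / 60 = 5%, as stated.
- Control need: 10 × 3 = 30 doses. Appendix D gives no stock or spares for them.

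**2. Roles side by side.**

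| Task | Assigned to | May know the arm under Method of blinding? |
| --- | --- | --- |
| Prepare vaccine | Preparers | Yes |
| Use a replacement dose (6.3.3) | Person in charge of the vaccination | Not stated to be a preparer |
| Record use and reason on CRF and accountability form (6.3.3) | Investigator | No |
| Detect adverse events, judge causality (8, 8.3) | Investigator | No |
| Sign for supplies (Appendix D, item 3) | Investigator or pharmacist | Not if an investigator who rates safety |

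The conflict is in the third and fourth rows, where the same role records replacements and rates safety. No unblinded delegate is named and no masking of the form is described.

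**3. What an entry can disclose.**
- Reason refers to the adjuvant vial: Group 3, because only that arm has one (section 6.2).
- Reason refers to the control vaccine's diluent: Group 4.
- A lot number is written down: section 6.2 prints the Group 3 antigen lot, so the number can be decoded from the protocol itself.
- The form shows FMP010 or AS01B stock falling for a given volunteer: Group 3.
- A neutral entry, saying only that a dose was unusable and was replaced: nothing from the CRF page. What the form discloses depends on its layout, which the protocol does not show.

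**4. Number of Group 3 volunteers exposed, from the listed spares.**
- Every spare used for a different volunteer: 3 + 3 = 6, which is 6 / 20 = 30% of Group 3 and 6 / 30 = 20% of the trial.
- Antigen and adjuvant always replaced as a pair: 3, which is 3 / 20 = 15% of Group 3.
- No replacement needed: 0.

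A replaced control dose could also be disclosed, but with no Rabipur spares listed the documents give no figure from which to bound that number.

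**The case against.** The strongest reply is that the two descriptions answer different questions. Section 5.4 says how the replacement is identified; section 6.3.3 says who uses it and how its use is documented. One person can do both: open the envelope, use the dose it designates, record it. Section 6.3.3 asks for the use and the reason, not the product or lot. The Method of blinding rule governs everything else, an unblinded delegate could make the entry, and a pharmacist may sign for supplies. Erythema, swelling and fever are graded on measured cut-offs, and the sample-size section expects a mainly descriptive safety analysis.

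Much of this stands. A reader might infer that the two procedures contradict each other. They do not, since both can be followed; they are unreconciled and lack a cross-reference.

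A reader might also infer that the investigator keeps these records next to vials carrying the volunteer's number, because section 6.2 says "Vaccine and adjuvant vials will be labeled with subject identifier and saved until study completion" and Appendix D has box labels with "study number, subject number, lot number, and instructions for vaccine administration". The text does not say so. Under section 6.3.3 spent vials "will be retained separately for confirmation of correct dosing if need be", and no custodian is named. The further inference that all 30 volunteers are identifiable needs raters to have access to the stored vials or boxes, and no section grants it.

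The recording duty itself is not answered. Section 6.3.3 names the investigator, requires a reason, and covers replacement of adjuvant as well as vaccine. A general rule that raters stay blind does not cure a specific instruction that can defeat it. A mainly descriptive analysis still depends on blinded intensity and causality judgements.

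**Conclusion.** The concern holds in a limited form. Section 6.3.3 gives a potentially arm-revealing record to the person who rates safety, which conflicts with the rule that only preparers know the assignment. It also leaves out the envelope safeguard in section 5.4. The exposure is confined to volunteers with a replaced dose: from the listed spares, at most about 6 of 20 in Group 3 and possibly none.

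That range assumes that the listed spares are the only Group 3 replacement stock and that each is used at most once. Actual disclosure also depends on what is written as the reason and on the layout of the CRF page and form, neither of which is shown. The point should be corrected because it touches the blind on the primary endpoints and is a stated conduct instruction, not a detail left to an analysis plan. It does not show that the trial's blind fails as a whole.

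**What to change.** - **Sections 5.4 and 6.3.3:** write one replacement procedure. The envelope designates the replacement; the unblinded preparers select it, log the reason and complete the accountability form.
- **CRF:** the page that the investigator completes records only that the dose was given and whether it was replaced (yes or no), with no product, lot number or product-specific reason.
- **Appendix D, item 3:** assign receipt and reconciliation of supplies to the pharmacist or a preparer, not to an investigator who rates safety.
- **Cross-reference:** section 6.3.3 sends the reader to Appendix E for supplies; these are in Appendix D.

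The cost is wording in these sections, an adjusted CRF page and a change in who completes the form. The preparers already exist under section 5.4, so no staff, visits or volunteers are added.

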# Concomitant medication/treatment

At each study visit/contact, the investigator will question the subject or their legal representative about any medication taken. Any immunosuppressants or other immune-modifying drugs or treatments, any vaccine other than the study vaccine(s) and any antipyretics administered at ANY time during the period starting 30 days prior to the first dose of study vaccine(s) and until study completion must be recorded in the CRF with trade name and/or generic name of the medication, medical indication, total daily dose, route of administration, start and end dates of treatment. Any other concomitant medication administered prophylactically in anticipation of reaction to the vaccination must also be recorded in the CRF with trade name and/or generic name of the medication, total daily dose, route of administration, start and end dates of treatment and coded as ‘Prophylactic’.

# ADVERSE EVENTS

The investigator is responsible for the detection and documentation of events meeting the criteria and definition of an adverse event (AE) or serious adverse event (SAE) as provided in this protocol. During the study, when there is a safety evaluation, the investigator or site staff will be responsible for detecting AEs and SAEs, as detailed in this section of the protocol. Each subject will be instructed to contact the investigator immediately should they manifest any signs or symptoms they perceive as serious.

## Eliciting and documenting adverse events

### Adverse event definition

An AE is any untoward medical occurrence in a study volunteer, temporally associated with the use of a test article, whether or not considered related to the test article. An AE can therefore be any unfavorable and unintended sign (including an abnormal laboratory finding), symptom, or disease (new or exacerbated) temporally associated with the use of a test article whether or not it is considered to be study related.

Examples of an AE include:

- Exacerbation of a chronic or intermittent pre-existing condition including either an increase in frequency and/or intensity of the condition.
- New conditions detected or diagnosed after investigational product administration even though it may have been present prior to the start of the study.
- Signs, symptoms, or the clinical sequelae of a suspected overdose of either investigational product or a concurrent medication (overdose per se should not be reported as an AE/SAE).
- Signs, symptoms temporally associated with vaccine administration.

AEs may include pre- or post-treatment events that occur as a result of protocol-mandated procedures (i.e., invasive procedures, modification of subject’s previous therapeutic regimen). Pre-existing conditions or signs and/or symptoms present in a subject prior to the start of the study (i.e. prior to the first study procedure) as well as any that are not recognized at study entry but are recognized during the study period, should be recorded in the medical history section of the subject’s CRF. Adverse events that occur after informed consent is obtained, but prior to vaccination, will be documented the Medical History form within the participant's CRF. Anticipated day-to-day fluctuations of pre-existing conditions, including disease under study, that do not represent a clinically significant exacerbation need not be considered adverse events. Adverse events should be documented in terms of medical diagnosis(ses) when possible. When this is not possible, the adverse event should be documented in terms of signs and symptoms observed by the investigator or reported by the participant at each study visit.

Although not considered as an adverse event, hospitalization for either elective surgery related to a pre-existing condition that did not increase in severity or frequency following initiation of the study, or for routine clinical procedures (including hospitalization for “social” reasons) that are not the result of an adverse event, must be recorded in the CRF. If the hospitalization arises from a pre-existing condition, or was planned prior to the first vaccination, it should be recorded in the Medical History form of the CRF. If the hospitalization arises from a pre-existing condition, and the hospitalization was planned after the first vaccination, it should be recorded in the adverse event page of the CRF. In both cases, it should be recorded as ‘Hospitalization,’ and the relationship to vaccination will be checked “No.”

*Surveillance period for occurrence of adverse events*

All adverse events occurring within one month (minimum 30 days) following administration of each vaccine must be recorded on the Adverse Event form in the participant's CRF, irrespective of severity or whether or not they are considered vaccination-related. See Section 8.5 for instructions for recording and reporting of serious adverse events.

*Recording adverse events*

At each visit/assessment, all adverse events either observed by the investigator or one of his clinical collaborators or reported by the participant spontaneously or in response to a direct question will be evaluated by the investigator. Adverse events not previously documented in the study will be recorded in the Adverse Event form within the participant's CRF. The nature of each event, date and time (where appropriate) of onset, outcome, intensity, and relationship to vaccination should be established. Details of any corrective treatment should be recorded on the appropriate page of the CRF.

Adverse events already documented in the CRF, i.e. at a previous assessment, and designated as ‘ongoing’ should be reviewed at subsequent visits, as necessary. If these have resolved, the documentation in the CRF should be completed.

N.B. If an adverse event changes in frequency or intensity during a study period, the highest intensity will be recorded. If the adverse event recurs with a defined interval of symptom-free time (>24 hours) in between episodes, new record of the event will be started.

Events that are not alarming and may reasonably be regarded as caused by or probably caused by the vaccine should be batched together and reported to the DHSP/WRAIR IRB and Sponsor’s Representative at the time of continuing review. See Section 8 for instructions for reporting and recording of unanticipated problems involving risk to others and/or serious adverse events.

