## Study Endpoints

**Co-primary endpoints**

- Occurrence and intensity of solicited symptoms on day of vaccination plus days 1, 2, 3 and 7 and after each vaccination
- Occurrence and intensity of unsolicited symptoms over a 30-day follow-up period (day of vaccination plus 29 subsequent days) after each vaccination
- Occurrence of serious adverse events (SAEs), defined IAW 21 CFR 312.32(a), during the study period.

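### Section 8.1.1 gives two conflicting rules for a condition that may pre-date the study but is first recognised after vaccination, so unsolicited events can be under-counted or filed inconsistently

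*Protocol*

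**What the plan says.** Protocol section 8.1.1 (Adverse event definition) deals with this case twice.

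- The list of examples of an adverse event includes "New conditions detected or diagnosed after investigational product administration even though it may have been present prior to the start of the study".
- The paragraph after the list covers "Pre-existing conditions or signs and/or symptoms present in a subject prior to the start of the study". It then widens this group with the words "as well as any that are not recognized at study entry but are recognized during the study period", and assigns the whole group to the CRF's medical history pages.

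The same section has a separate sentence for the interval before dosing: "Adverse events that occur after informed consent is obtained, but prior to vaccination, will be documented the Medical History form". Under the surveillance-period heading, adverse events in the month after each dose "must be recorded on the Adverse Event form in the participant's CRF, irrespective of severity or whether or not they are considered vaccination-related".

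The endpoint that depends on this is the second co-primary endpoint (synopsis and sections 2.2 and 10.2): "Occurrence and intensity of unsolicited symptoms over a 30-day follow-up period (day of vaccination plus 29 subsequent days) after each vaccination". Section 8.1.3 defines unsolicited symptoms as a kind of adverse event. Section 10.4.2 tabulates subjects with at least one unsolicited adverse event by coded term, per group and dose.

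**The concern.** Suppose a volunteer is found after Dose 1 to have a condition that could have been there before enrolment. Under the example list it is an adverse event. Under the following paragraph it belongs in medical history. Two assessors could file the same finding on different forms and both comply with the protocol.

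The endpoint is built from what is classed as an adverse event, so an entry made only in medical history drops out of a co-primary count. Section 10 expects the safety analysis to be mainly descriptive. The counts are then the result, and no later test or model would recover an event filed elsewhere. Nor is this a detail that an analysis plan can settle afterwards, because the form is chosen at the site when the finding is made.

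**Working it through.** The protocol states no figure on this point, so the check is mainly a comparison of texts.

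**Which cases meet both rules**

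| Case | Example list, 8.1.1 | Medical history sentence, 8.1.1 | Conflict? |
| --- | --- | --- | --- |
| Clear onset after vaccination | Adverse event | Does not apply (limited to pre-existing conditions) | No |
| Exacerbation of a known condition | Adverse event (first example) | Does not remove it | No |
| Event between consent and Dose 1 | Does not apply | Medical History form, by its own sentence | No |
| Was or may have been present before the study, first recognised after a dose | Adverse event | Medical history | **Yes** |

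**Whether other text settles the last row**

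- The sentence on events between consent and vaccination covers only the time before dosing.
- The 30-day rule requires every adverse event on the Adverse Event form whatever its cause. It applies only once the finding has been classed as an adverse event, which is the open question.
- Section 8.3, on laboratory and other abnormal assessments, reports clinically significant abnormalities detected during the study as adverse events. This agrees with the example list but does not cover symptoms and diagnoses in general.

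None of these says which rule prevails or that both forms are to be completed.

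**Scale of one case**

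Inputs: 20 subjects in Group 3 and 10 in Group 4 (synopsis), with minimum enrolment of 16 and 8 (section 5.3, Study Design). The shift from one subject is 100/n percentage points.

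| Group | Planned n | Shift | Minimum n | Shift |
| --- | --- | --- | --- | --- |
| 3 | 20 | 100/20 = 5 points | 16 | 100/16 = 6.25 points |
| 4 | 10 | 100/10 = 10 points | 8 | 100/8 = 12.5 points |

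For orientation, the exact (Clopper-Pearson) 95% intervals at planned size are:

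- Group 3: 0/20 gives 0 to 16.8%; 1/20 gives 0.1 to 24.9%.
- Group 4: 0/10 gives 0 to 30.8%; 1/10 gives 0.3 to 44.5%.

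**When the shift occurs**

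The table counts subjects with at least one event. A misfiled entry therefore changes a row only if that subject has no other event in it. Section 1.3.2 reports that 96% of volunteers in the earlier western Kenya adult study had an unsolicited event within 30 days of vaccination. If that rate carried over, the expected number of subjects with no recorded event would be 20 × 0.04 = 0.8 in Group 3 and 10 × 0.04 = 0.4 in Group 4. The any-event total would then rarely move. A row for a single preferred term or a single dose holds fewer events per subject, so a full 5- or 10-point shift is more likely there.

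**The case against.** The best defence is that the two sentences can be partly reconciled. The example concerns conditions that only may have been present earlier. The medical history sentence concerns conditions that were present. On that reading, uncertain onset gives an adverse event and established prior presence gives medical history. This narrows the overlap but does not remove it. The form used still turns on a judgement made after dosing, for which the protocol gives no criterion.

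A second defence stands in part. The medical history sentence does not forbid an entry on the Adverse Event form as well. Elsewhere, when the protocol means to exclude something from adverse events, it says so expressly. Completing both forms would comply with everything written, so loss from the count is possible and not certain.

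Third, the pool of cases may be small. Screening includes history, examination and laboratory tests, partly repeated on Day 0, and section 8.3 already captures clinically significant abnormal assessments.

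A reader might infer two stronger claims that the documents do not support.

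- That any condition first found after vaccination is sent to medical history and taken off the Adverse Event form. The clause refers back to pre-existing conditions only, and it does not say that the entry replaces one on the Adverse Event form.
- That the choice biases the comparison between groups. The section on the method of blinding keeps endpoint evaluators unaware of allocation and masks the syringes. Visible or reported local reactions might reveal some allocations: pain followed 81.0% of RTS,S/AS01B doses in the earlier US study (section 1.3.2). Nothing in the protocol, however, links local reactions to decisions about medical history.

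**Conclusion.** The conflict is real and lies in the current text of one section. It is limited to conditions that were or may have been present before the study and are first recognised after a dose. For those, the protocol gives two destinations and no order of precedence. The foreseeable effects are under-counting of unsolicited adverse events, a co-primary endpoint, and inconsistent filing between assessors. Between-group bias remains possible but is not shown.

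The number of affected cases cannot be obtained from the protocol. The 5-point and 10-point shifts rest on two assumptions: that the case is entered in medical history only, and that it is the subject's sole event in the row concerned. No test or decision threshold in the protocol depends on the classification. The point is therefore a worthwhile correction of wording and not a threat to the design.

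**What to change.** State one rule in section 8.1.1. The smallest change is to delete the clause "as well as any that are not recognized at study entry but are recognized during the study period". Amending it is safer, because the rest of the sentence could still be read as covering a condition that was present before the study and found later. The amended text should say three things:

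- A condition first detected or diagnosed after Dose 1 is recorded on the Adverse Event form. This agrees with the example list, the 30-day recording rule and section 8.3.
- Any suspected earlier onset is entered in the onset field, which the form already has.
- If wanted, the condition is also noted in medical history, in addition to the Adverse Event entry and not in place of it.

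Two further steps are not needed. Restricting medical history to conditions documented before Dose 1 would turn old history that a volunteer mentions late into an adverse event. Using the causality item to record earlier onset would not work well, because section 8.3 makes it a yes/no question about the vaccine's contribution.

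The cost is one amended sentence and a few more unrelated adverse events in the listings.
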